**d. Number of Triggering Events in Ten Active Fists**

Number of Triggering Events in Ten Active Fists will be used to measure the patient's triggering frequency (Finch et al. 2002). The number of triggering events (0 – 10) can be obtained by asking the patient to make 10 active full fists (Colbourn et al. 2008). Typically, this involves asking the patient to actively and fully open and close the fingers 10 times. If the finger persistently locks anytime during active finger opening and closing, a score of 10/10 will be assigned. If the patient has multiple TF per hand, he/she is only asked to open and close the fingers 10 times. The result is taken from the worst finger's performance. Time needed to make 10 active full fist will be recorded using a stopwatch or clock that reads in seconds.

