### 3.8 Study Visits and Procedures

This study will adopt a randomized comparative trial design. This study will involve the researcher, a counter staff, Therapist A, and Therapist B. The researcher will do the eligibility screening and splint fabrication. The counter staff will be involved in random assignment of participants to either the RMG or the MCPJBG. Therapist A, an occupational therapist with 10-years of experience is not a research team member and will conduct the pre-intervention assessments at Day-1 and the post-intervention assessments at Week-6. Therapist B, a senior occupational therapist with 20-years of experience also is not a research team member and will involve in conducting the conventional therapy program and assessment at Week-3. Due to the nature of study and the visibility of splint wearing (Jackman et al. 2013), the participants, the researcher, Therapist A, and Therapist B will not be blinded to the intervention.

Patients who have been recently diagnosed as having TF involving the A1 pulley and referred by the Orthopaedic Clinic, Hospital Sultan Haji Ahmad Shah to the hospital's Occupational Therapy Unit will make a new patient appointment for occupational therapy. Therapy will be provided at the Occupational Therapy Unit. Patients with TF will have a designated appointment and will be registered in the hospital information system as a new outpatient by the counter staff. The researcher will receive notice of a potential participant through the hospital information system on registration, and a preliminary screening of each potential patient will be done by the researcher. This screening will include review of the electronic referral letter and the past electronic medical records entered by the orthopaedic surgeon. After the preliminary screen of the records, the researcher will ask the potential participant additional questions according to inclusion and exclusion criteria to insure study eligibility.

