Once study eligibility is confirmed, the researcher will provide the information sheet and explain the study to the potential patient. If the patient agrees to participate, he/she will then be asked to sign the informed consent form and assigned an Identity Number (ID) for anonymity purposes. After signing the informed consent form, the Therapist A will proceed to administer the Demographic Questionnaire and other pre-intervention (baseline) assessments i.e., SST, DASH, COPM, VAS (pain, comfort, and satisfaction), and the Number of Triggering Events in Ten Active Fists. After completing the pre-intervention assessments, the participant will be asked to go to a designated counter near the therapy room for simple random assignment to the RMG or MCPJBG. Assignment will be done via concealed allocation with selection of an envelope by the counter staff. The envelope is prepared by the researcher. The envelope will contain either a paper printed with A which indicates RMG and B which indicates MCPJBG. After the participant returning to the therapy room, he/she will give the group assignment paper to the researcher. The researcher will fabricate either the RM splint or MCPJ blocking splint based on the randomization of group allocation. Each type of splint, the RM splint and MCPJ blocking will be fabricated using a low temperature thermoplastic material with 3.2 mm thickness, 1% perforation, and 100% memory.

For participants assigned to RMG, either a RME splint or a RMF splint will be fabricated. The splint design will be dependent on the participant's response to the RM pencil test carried out by the researcher. For this study, the RME pencil test will require the researcher to weave the pencil under the proximal phalanx of the affected finger(s) and over the dorsum of the adjacent fingers' proximal phalanx. For the RMF pencil test the researcher will weave the pencil over the dorsum of the proximal phalanx of the affected finger(s) and under the proximal phalanx of the adjacent fingers. With the pencil in place, the participant will be asked to open and close their fingers several times. The participant will be asked to choose which pencil test, RME or RMF lessened their pain and/or triggering. If the answer is the RME position, then a RME splint will be prescribed. Conversely, if the answer is the RMF position, then a RMF splint will be prescribed.

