Each participant will be required to attend three sessions of therapy over the study period of six weeks. These sessions ideally will be the initial therapy session (Week-1), then three weeks later (Week-3), and six weeks after the initial session (Week-6). At Week-3, Therapist B will conduct the VAS assessment (comfort, and satisfaction) and provide the conventional therapy to each participant. Therapist B will perform a deep circular massage over A1 pulley for 5 minutes and each participant will be taught how to do the deep circular massage at home. The researcher will inspect each participant's splint and adjust it accordingly based on the participant's comments.

At Week-6, Therapist A will administer the post-intervention assessment for all participants. Table 1.0 outlines the procedure involved in RMG and MCPJBG. Figure 1.0 is the flowchart of the procedure.

Table 1.0 Procedure involved in Relative Motion Group and Metacarpophalangeal Joint Blocking Group.

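### Therapist A is left unblinded because the splint is visible, although SST stage and the triggering count could be masked at almost no cost

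*Protocol*

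**What the plan says.** Section 3.8 gives one shared reason, "Due to the nature of study and the visibility of splint wearing", for leaving four parties unblinded: "the participants, the researcher, Therapist A, and Therapist B will not be blinded to the intervention". No reason specific to Therapist A is given, and no masking of Therapist A is described anywhere.

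The same section describes Therapist A as an occupational therapist who "is not a research team member and will conduct the pre-intervention assessments at Day-1 and the post-intervention assessments at Week-6". Other people hold the tasks that need the allocation:

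- Baseline comes first: "After completing the pre-intervention assessments, the participant will be asked to go to a designated counter near the therapy room for simple random assignment".
- The allocation paper goes to the researcher: "The researcher will fabricate either the RM splint or MCPJ blocking splint based on the randomization of group allocation".
- At Week 3, "Therapist B will conduct the VAS assessment (comfort, and satisfaction) and provide the conventional therapy to each participant", and the researcher inspects and adjusts the splint.
- "At Week-6, Therapist A will administer the post-intervention assessment for all participants".

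Section 3.1.1 d defines the triggering outcome: "The number of triggering events (0 – 10) can be obtained by asking the patient to make 10 active full fists". Section 3.1.1 b defines SST as a six-stage grading of finger movement.

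**The concern.** SST stage and the triggering count are observed and scored by a therapist. The other five outcomes (pain, DASH, COPM, comfort, satisfaction) are scored by participants who know which splint they wear. In an open splint trial, the observer-rated outcomes are therefore the only ones that can be kept free of the rater's expectations.

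SST requires a judgement between uneven movement, triggering, and the grades of locking. A therapist who knows the arm may lean one way at the boundaries. If Therapist A is unblinded, none of the seven hypotheses rests on a masked rating, although the staffing already supplies an independent assessor.

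**Working it through.** The protocol gives no figure on this point to reproduce. The check traces each stage at which Therapist A might learn the allocation.

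1. **Day 1, before assignment (3.8).** Therapist A gives the demographic questionnaire and baseline assessments before the envelope is drawn. The allocation cannot be known yet.
2. **Day 1, fabrication (3.8).** The researcher receives the allocation paper, runs the pencil tests in the RM arm and makes the splint. Therapist A has no task here. The participant does return to the therapy room, however, and nothing says that Therapist A is absent.
3. **Day 1, splint ratings (3.8, Table 1.0, VAS forms).** The comfort and satisfaction VAS are listed in the baseline set given to Therapist A. The form items ask about the splint being worn, and 3.8 has participants rate it after fitting, before leaving the clinic, without naming who collects the rating. If Therapist A collects it, the splint is seen on Day 1.
4. **Week 3 (3.8).** Therapist B collects comfort and satisfaction and treats; the researcher adjusts the splint. Therapist A has no role.
5. **Week 6 (3.8, Table 1.0).** Therapist A carries out all post-intervention assessments. A participant who arrives wearing the splint reveals the arm.

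No step gives Therapist A a task that requires knowing the arm. Exposure is certain at neither visit, but possible at two: Day 1 after fitting, and Week 6.

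**Can the splint be off at Week 6?** Section 3.8 already allows removal for hygiene, so the splint is physically removable. Section 3.1.1 d asks for full opening and closing of the fingers, while section 1.1 says that the MCPJ blocking splint is meant to stop MCPJ motion completely. A full fist is not possible in that splint, so the test itself implies that it is off. The baseline test is made before any splint exists.

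**Which outcomes gain?** Of the seven hypotheses in section 2.1, two are assessor-rated (1, SST; 3, triggering). The other 7 − 2 = 5 are participant-rated. COPM is scored by the participant, but in an interview that Therapist A conducts.

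**Illustration only.** The bias δ, in SD units, is assumed; nothing in the protocol supports a value. Section 3.6 needs 32 participants before dropout, so n = 16 per arm. For a two-sided two-sample t-test at 5% with no true difference, df = 30, the critical value is 2.042 and the noncentrality is δ√(n/2) = δ√8:

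- δ = 0.2: 0.566, rejection rate 0.085
- δ = 0.3: 0.849, rejection rate 0.130
- δ = 0.5: 1.414, rejection rate 0.278

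Section 3.9 plans a two-way mixed ANOVA instead. Take two time points, equal SDs, bias at Week 6 only, δ = 0.5, and an assumed pre-post correlation r:

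- Group-by-time interaction, shift δ/√(2(1 − r)): r = 0.3, 0.5, 0.7 gives 0.423, 0.500, 0.645 SD and rejection rates of 21%, 28%, 42%.
- Group main effect, shift (δ/2)/√((1 + r)/2): the same r give 0.310, 0.289, 0.271 SD and rates of 14%, 12%, 12%.

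The t-test figures match the interaction test only at r = 0.5. The result depends on δ, on r and on which effect is read, and none of these can be settled from the protocol.

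**The case against.** The strongest case for leaving the text alone has four parts.

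*The choice is disclosed and reasoned.* Open assessment is common where the device is visible, and the protocol contradicts nothing by saying so. That stands, which is why this is an improvement to the design and not an error. The stated reason still does not reach Therapist A.

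*The benefit is limited.* Pain, on which section 3.6 bases the sample size, is among the five outcomes that masking Therapist A would not protect. The triggering count also leaves the rater limited room: it runs from 0 to 10, persistent locking scores 10, and the worst finger is taken. Both points stand.

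*Masking may leak.* Skin marks, chance remarks and above all a COPM interview about daily activities after six weeks of full-time wear may reveal the arm. This stands too. It argues for doing SST and the ten fists first, and for recording the assessor's guess.

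*Harm is not demonstrated.* Correct: the size of any bias is an assumption.

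A reader might also infer more than the text supports:

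- That Therapist A meets participants only before randomisation and at Week 6, so that a change at Week 6 is enough. The Day-1 comfort and satisfaction ratings leave this unsecured.
- That the ten-fist test is made in the splint, so that the arms perform different tests. The protocol does not say so, and the requirement for full fists implies the contrary. Stating splint-off is a clarification.

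**Conclusion.** The point holds as a cheap, worthwhile improvement. Section 3.8 gives up masking of Therapist A for a reason that does not apply to Therapist A's tasks. Masking is feasible for SST stage and the triggering count, two of the seven hypotheses, provided that Day 1 as well as Week 6 is covered. It would not protect pain, DASH, COPM, comfort or satisfaction.

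The false-positive rates above should not be read as a forecast for this trial. They show only that, at about 16 per arm, a moderate systematic shift in ratings could matter.

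The conclusion rests on two readings of the text: that Therapist A has no duties beyond those in 3.8, and that the therapist scores SST and triggering.

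**What to change.** Amend section 3.8 and Table 1.0 so that Therapist A is masked to allocation; participants, the researcher and Therapist B remain unblinded.

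- **Day 1.** Take comfort and satisfaction VAS out of Therapist A's baseline set. Have them self-completed after fitting and collected by someone else. State that Therapist A is not present at fabrication.
- **Week 6, on arrival.** The participant removes the splint, leaves splint and diary outside the room, and is asked not to name the splint. Section 3.8 currently names only hygiene as grounds for removal and bars gripping out of the splint, so the amendment should say how the assessment fits with that instruction.
- **Week 6, order.** Therapist A does SST and the ten fists first, splint off in both arms, then the COPM interview.
- **Week 6, splint ratings.** Comfort and satisfaction VAS are self-completed away from Therapist A, with the splint on or off in the same way as at the earlier visits.
- **Check on masking.** Therapist A records a guess of the group, to be reported by arm.

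The cost is a few extra minutes and some handling by existing staff. Treatment, sample size and outcomes do not change. Some participants will still be unmasked.

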For the RME splint, a strip of thermoplastic will be woven around on the proximal phalanx of all four fingers with the MCPJ of the affected finger(s) positioned in approximately 20°-25° more extension than MCPJ of the adjacent fingers. For the RMF splint, the thermoplastic strip will be woven with the MCPJ of the affected finger(s) positioned in approximately 20°-25° more flexion than the MCPJ of the adjacent fingers. The angle of MCPJ will be increased if 20°-25° flexion/extension is not enough to reduce/stop pain or triggering. For MCPJ blocking splint, the thermoplastic material will be moulded to contour the palm over the MCPJ and formed into a circumferential "ring" around the proximal phalanx of the affected finger(s). After the splint was fabricated, the participants will have to wear the splint for 15 minutes to check if the splint has pressure points that can cause pain or any redness of the skin. If there are pain and redness, the splint will be readjusted to prevent these pressure points. For all splints, each participant will be asked to assess the comfort and satisfaction with the splint before leaving the clinic.

The RMG and MCPJBG participants will receive same education and conventional treatment. Each participant will be instructed to wear the splint full time (24-hours) every day and night for six weeks, with the exception that the splint can be removed for hygiene purposes including washing hands and showering. No gripping when out of splint. To track splint wearing adherence, each participant will be given a diary to record the hours the splint was worn in a 24-hour period. Participant will also be asked to record what task(s)he/she has

removed the splint. Each participant will be informed about the condition of TF including symptoms, cause, risk factor, and treatment. Participants will also be encouraged to modify activities that may provoke their TF symptoms while wearing the splint. Suggestions for activity modification include stopping or limiting activities that involve repetitive hand use and prolonged gripping. Participants will be asked to contact the researcher if there are any problems with the splint that affect wear or to replace the splint if participant has accidentally lost their splint. The researcher will arrange an appointment as soon as possible with them to address these problems and make note of this interruption in intervention.

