| Week 1 (Day 1)
Assessment 
 
Demographic questionnaire
 
Pre-intervention assessments               
 
DASH
 
COPM
 
VAS (Pain, Comfort, & Satisfaction)
 
Number of Triggering Events in Ten Active Fists
 
SST
 
 
 

Splint 
 
RME pencil test
 
RMF pencil test
 
Fabricate RME splint or RMF splint
 
MCPJ of the affected finger is approximately 20°-25° extension/flexion than the MCPJ of the adjacent fingers
 
Increase the angle if 20°-25° MCPJ extension/flexion of affected finger is not enough to reduce/stop the triggering/pain
 

Patient Education 
 
Splint wear full time for 6 weeks, only remove for hygiene purpose
 
No gripping when out of splint
 
Provide a diary to record everyday splint wear duration (hours)
 
Record what task the splint is removed for
 
About TF condition
 
 | Week 1 (Day 1)
Assessment 
 
Demographic questionnaire
 
Pre-intervention assessments               
 
DASH
 
COPM
 
VAS (Pain, Comfort, & Satisfaction)
 
Number of Triggering Events in Ten Active Fists
 
SST
 
 
 

Splint 
 
Fabricate MCPJ blocking splint
 
MCPJ positioned at 0°
 

Patient Education 
 
Splint wear full time for 6 weeks, only remove for hygiene purpose
 
No gripping when out of splint
 
Provide a diary to record everyday splint wear duration (hours)
 
Record what task the splint is removed for
 
About TF condition
 
Reduce or avoid activities such as repetitive hand use and prolonged grip or any action that causes pain/triggering
 
 |

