### 3.9 Statistical Analysis Plan

Descriptive statistics will be used to summarize the Demographic data including age, gender, occupation, hand dominance, digit involved, associated medical conditions, and duration of triggering. Data will be analysed and described in total numbers, mean, and the pattern of data. Descriptive statistics will also be used to demonstrate the assessment outcomes including DASH, COPM, VAS (pain, comfort, and satisfaction), Number of Triggering in Ten Active Fists, and SST. An independent sample *t*-test, set at the significant level of 0.05 will be used to compare the baseline data between RMG and MCPJBG. A Two Way Mixed-ANOVA, set at the significant level of 0.05 will be used to compare the assessment outcomes, including DASH, COPM, VAS (pain, comfort, and satisfaction), Number of Triggering in Ten Active Fists, and SST between the RMG and MCPJBG. The interaction effect between these different variables will be analysed too. The results will show the percentage of variance in each effect regardless of size (Hypotheses 1 – 7).

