**VISUAL ANALOG SCALE (WEEK-1 / WEEK-3 / WEEK-6)**

**SPLINT WEARABILITY: COMFORT**

Are you comfortable with splint that you are wearing at rest?  
(Adakah anda selesa dengan splint yang anda pakai semasa anda sedang berehat?)

[figure not shown]

Are you comfortable with splint that you are wearing while performing activities?  
(Adakah anda selesa dengan splint yang anda pakai semasa anda melakukan aktiviti?)

[figure not shown]

Notes (Catatan): .....

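### Comfort and satisfaction with the splint are scheduled as baseline ratings before any splint exists, so Hypotheses 6 and 7 have no valid Day-1 baseline and no clearly defined test

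*Protocol*

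**What the plan says.** **Order of events on Day 1 (Protocol 3.8).** After consent, Therapist A gives the "other pre-intervention (baseline) assessments i.e., SST, DASH, COPM, VAS (pain, comfort, and satisfaction), and the Number of Triggering Events in Ten Active Fists". Then: "After completing the pre-intervention assessments, the participant will be asked to go to a designated counter near the therapy room for simple random assignment". Then: "The researcher will fabricate either the RM splint or MCPJ blocking splint based on the randomization of group allocation". Table 1.0 follows the same order. It lists comfort and satisfaction in the pre-intervention block for Week 1 (Day 1), ahead of the splint block, and shows no separate post-fitting rating.

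**A second Day-1 rating (also 3.8).** After fabrication and a 15-minute trial wear: "For all splints, each participant will be asked to assess the comfort and satisfaction with the splint before leaving the clinic".

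**The form.** The comfort item reads "Are you comfortable with splint that you are wearing at rest", and the satisfaction items are worded in parallel. The form covers Week 1, Week 3 and Week 6, with a single Week-1 occasion.

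**Analysis (3.9).** An independent-samples t-test compares the baseline data between groups. Then: "A Two Way Mixed-ANOVA, set at the significant level of 0.05 will be used to compare the assessment outcomes". Comfort and satisfaction are in that list with no exception. The comparison is described as being between the two groups, and the interaction is to be analysed as well.

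**Objectives 6 and 7 (2.2.2)** ask for the comparison of the splints on comfort and on satisfaction after six weeks.

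**The concern.** Pain, DASH, COPM, triggering count and SST all have a genuine pre-splint value. Comfort and satisfaction with a splint do not. Two Day-1 measurements are prescribed, the form has room for one, and nothing says which of them enters the analysis as baseline.

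Neither will serve. A rating made before randomisation has no splint to refer to. A rating made after fitting is a post-randomisation response to the allocated device: the baseline t-test then tests a treatment effect, and any change-from-Day-1 contrast removes whatever part of that effect is already present.

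At stake are two of the seven hypotheses. Section 1.2 names patients' perception of wearability as one of two evidence gaps behind the trial.

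**Working it through.** **1. The Day-1 value under each reading**

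| Reading | When rated | Splint worn? | What the value is |
|---|---|---|---|
| Pre-intervention list in 3.8, Table 1.0 | before randomisation and fabrication | no | unanswerable on this form |
| Post-fitting instruction in 3.8 | after 15 minutes of wear | yes, the allocated one | a treatment outcome |

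**2. The plan's own figure.** Section 3.6 gives pain 4.65 (SD 2.39) before and 3.40 (SD 2.44) after treatment, f = 0.26 and N = 32.

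- d = (4.65 − 3.40)/√((2.39² + 2.44²)/2) = 1.25/2.415 = 0.518; f = d/2 = 0.259. Both match.
- For a group-by-time interaction with 2 groups and m = 2 times, λ = f²·N·m/(1 − ρ). With ρ = 0.5 (assumed; the protocol gives none), λ = 0.0676 × 32 × 2/0.5 = 8.65 on 1 and 30 df, and power is 0.812. So N = 32 is reproduced. With ρ = 0.3 it would be 44, and with ρ = 0.7 it would be 20.
- For the between-group term, λ = f²·N·m/(1 + (m − 1)ρ), which needs N = 90 at ρ = 0.5.
- 32/0.9 = 35.6, hence 36.

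The stated N fits an interaction calculation, but 3.6 does not name the term and the inputs are pain scores.

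**3. What each term can detect for comfort or satisfaction.** Inputs: 16 per arm (N = 32), two-sided α = 0.05, SD 1 at each visit, equal correlation ρ between visits, and a Week-6 difference Δ = 1 SD. Δ and ρ are assumptions, because the protocol gives no target difference or correlation for these outcomes. Let δ be the group difference in the Day-1 value. Standardised effects:

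- change from Day 1 (the interaction with two times): (Δ − δ)/√(2(1 − ρ))
- group main effect, two times: ((Δ + δ)/2)/√((1 + ρ)/2)
- group main effect, three times (Δ also at Week 3): ((2Δ + δ)/3)/√((1 + 2ρ)/3)
- Week 6 alone: Δ

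Power comes from the noncentral t with 30 df and noncentrality effect × √(16/2). Example: δ = 0.5 and ρ = 0.5 give a change effect of 0.5/1 = 0.5, noncentrality 1.41, power 0.278.

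| Day-1 value | ρ | Interaction, 2 times | Main effect, 2 times | Main effect, 3 times | Week 6 |
|---|---|---|---|---|---|
| Post-fitting, full difference (δ = 1) | 0.3 | 0.050 | 0.924 | 0.963 | 0.781 |
| | 0.5 | 0.050 | 0.885 | 0.918 | 0.781 |
| | 0.7 | 0.050 | 0.843 | 0.864 | 0.781 |
| Post-fitting, half (δ = 0.5) | 0.3 | 0.212 | 0.721 | 0.878 | 0.781 |
| | 0.5 | 0.278 | 0.659 | 0.798 | 0.781 |
| | 0.7 | 0.424 | 0.605 | 0.722 | 0.781 |
| Pre-splint, no difference (δ = 0) | 0.3 | 0.638 | 0.397 | 0.705 | 0.781 |
| | 0.5 | 0.781 | 0.352 | 0.608 | 0.781 |
| | 0.7 | 0.942 | 0.318 | 0.532 | 0.781 |

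A simulation of the mixed ANOVA (20,000 trials per setting) agrees to within about one percentage point. The pre-splint rows suppose that a mark made with no splint still correlates 0.3 to 0.7 with later ratings, which flatters the interaction.

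**4. The baseline t-test.** If Day 1 is post-fitting and δ = 1, it is the same calculation as the Week-6 test. It is significant in about 78% of trials, and a real splint effect would be read as baseline imbalance.

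**The case against.** The tempting stronger reading is that the planned analysis will cancel a real comfort advantage. The protocol does not support that.

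- Section 3.9 says the ANOVA compares outcomes between the groups and mentions the interaction as an addition. It never makes the interaction, or a Week-6-minus-Day-1 change, the deciding test for Hypotheses 6 and 7.
- A constant advantage from fitting onward is what the group main effect detects: 84–92% with two times and 86–96% with three, above the 78% of a Week-6 comparison.
- Cancellation needs three things together: the post-fitting rating as Day 1, the interaction as the test, and the difference already present after 15 minutes of wear.
- Linking N = 32 to the interaction for comfort is an inference. It depends on an assumed correlation of 0.5 and on pain data.
- The post-fitting instruction supplies an answerable Day-1 rating that fits the form's wording and its single Week-1 occasion, so the listing before randomisation may be a slip.
- Naming the deciding term is often left to a statistical analysis plan, which may exist.

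All of this stands, and it limits the point to a conditional one. It does not remove it. The protocol fixes the visit order, the form and the model, and these conflict. The main effect is no safe default either: if the pre-randomisation score is used as scheduled and carries no group difference, its power drops to 32–40% with two times, or about 53–70% with three.

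**Conclusion.** The point holds in this form: the Day-1 comfort and satisfaction value is either unanswerable or an outcome of the allocated splint, and section 3.9 treats it as an ordinary baseline. Each ANOVA term works under one reading of Day 1 and does badly under the other, and the protocol settles neither the reading nor the term. The between-group difference at Week 6 has about 78% power under every reading and is what Objectives 6 and 7 ask for.

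The percentages rest on an assumed 1 SD difference, 16 per arm and correlations of 0.3 to 0.7. They show how far the answer depends on an unstated choice and do not forecast this trial's power. The contradiction in timing needs no assumption. The other five outcomes have a valid pre-splint baseline and are unaffected. This should be fixed, but it does not invalidate the trial.

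**What to change.** 1. In 3.8 and in the Table 1.0 pre-intervention block, remove comfort and satisfaction from the assessments made before randomisation. Keep pain there.
2. Label the rating made after the 15-minute wear as Day 1 post-fitting in 3.8, Table 1.0 and the form heading, and treat it as an outcome.
3. In 3.9, exclude both variables from the baseline t-test.
4. In 3.9, state that Hypotheses 6 and 7 are tested by the between-group difference at Week 6. Day 1 post-fitting and Week 3 can be further outcome time points in a repeated-measures model, with no subtraction of, or adjustment for, the Day-1 rating.

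The cost is wording in two sections, one table block and one form heading. No participants or visits are added, and an assessment that cannot be answered as written is dropped.

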### 3.6 Sample Size

A sampling of convenient method will be used to select eligible patients.

A prior TF research study (Teo et al. 2019) had reported that the result of pain score for pre-treatment = 4.65 (SD 2.39) and post-treatment = 3.40 (SD 2.44). G\*Power was used to compute statistical power analyses. Cohen-d effect size is 0.5175152.

Given Cohen-d effect size needs to be converted into Cohen-f effect size in order to determine the sample size of this study for two ways ANOVA, therefore, after converting digitally, the Cohen-f effect size is 0.259.

This proposed study will need 32 participants when a Cohen-f effect size of 0.26, confident level of 95%, significant level of 5%, and statistical power of 80% is applied.

Since a 10% dropout rate is anticipated, a total of 36 participants will be needed for this study. Of this total, 18 patients will be allocated to the RM group (RMG) and 18 patients to the MCPJ blocking group (MCPJBG).

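### Allocation concealment is not secured against the recruiting researcher, who prepares the envelopes and receives every assignment; no sealing, opacity, numbering or independent sequence is stated

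*Protocol*

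**What the plan says.** All quotes below are from Protocol section 3.8 (Study Visits and Procedures) unless noted.

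- Screening and treatment: "The researcher will do the eligibility screening and splint fabrication".
- Consent: "the researcher will provide the information sheet and explain the study to the potential patient".
- Envelopes: "The envelope is prepared by the researcher".
- The draw: "Assignment will be done via concealed allocation with selection of an envelope by the counter staff". It takes place after the consent form is signed and after Therapist A, who is outside the research team, has completed the baseline assessments.
- After the draw, when the participant returns to the therapy room: "he/she will give the group assignment paper to the researcher".
- Blinding: "the participants, the researcher, Therapist A, and Therapist B will not be blinded to the intervention".
- Method: "simple random assignment to the RMG or MCPJBG".
- Section 3.6 (Sample Size), on group sizes: "18 patients will be allocated to the RM group (RMG) and 18 patients to the MCPJ blocking group (MCPJBG".

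Each envelope holds a paper marked A or B. The protocol does not say that the envelopes are sealed, opaque or numbered, how any sequence is generated, how many envelopes there are, or who keeps them between draws.

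**The concern.** Concealment means that whoever decides on entry cannot know or influence the next assignment. Here that person makes the envelopes. This procedure is fixed in the protocol; it is not a detail left to a later analysis plan.

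The stakes are raised by the rest of the design. Participants and assessors are unblinded, and five of the seven hypotheses rest on self-report (pain, DASH, COPM, comfort, satisfaction). Sound allocation is one of the few protections against bias that remain. Selection at entry cannot be reliably repaired in the analysis. Some discretion exists: section 3.6 describes convenience sampling, and the researcher settles eligibility by record review and questioning.

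The second, smaller question is whether simple randomisation and 18 per group describe the same procedure.

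**Working it through.** **1. Who does what (section 3.8)**

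| Task | Role |
|---|---|
| Screens eligibility | Researcher |
| Explains the study at consent | Researcher |
| Prepares envelopes | Researcher |
| Baseline assessment | Therapist A |
| Selects envelope | Counter staff |
| Receives assignment paper, makes splint | Researcher |

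Only the baseline assessment and the selection of the envelope lie outside the researcher's hands. With no sealing, opacity or numbering stated, nothing in the text stops the preparer from recognising, reordering or setting aside an envelope.

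**2. Simple randomisation against 18/18**

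Inputs: total N = 36 and 18 per group (section 3.6); each assignment A or B with probability 1/2.

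- P(exactly 18/18) = C(36,18) / 2^36 = 9,075,135,300 / 68,719,476,736 = 0.132. About 87% of trials would miss the stated split.
- P(14:22 or more unequal) = P(arm sizes differ by at least 8) = 0.243.
- Efficiency relative to equal arms = 4·nA·nB / N². At 14:22 this is 4×14×22 / 1,296 = 0.951; at 12:24 it is 4×12×24 / 1,296 = 0.889.

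Missing 18/18 is likely, but it costs little precision.

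**3. A fixed set of 18 A and 18 B, drawn in random order**

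Assume a researcher who has seen all past papers and always guesses the arm with more envelopes left, with n = 18.

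- Expected correct guesses = n + ½·(4^n / C(2n,n) − 1) = 18 + ½·(7.572 − 1) = 21.3 of 36, or 59%. Chance alone gives 18 of 36.
- Expected number of final assignments known with certainty = 2n / (n + 1) = 36 / 19 = 1.9.

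This is moderate predictability from counting alone. It leaves out anything learned by making the envelopes.

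**4. Permuted blocks of varied size**

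This remedy comes to mind first, so it was checked by simulation. The block sizes are assumptions, since the protocol names none. The guesser does not know them and guesses the arm currently behind, or tosses a coin when the arms are level; N = 36.

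| Scheme | Correct guesses from past assignments |
|---|---|
| Simple randomisation | 50% |
| One shuffled 18/18 list | 59% (21.3 of 36) |
| Blocks of 4, 6 or 8 | 68% |
| Blocks of 4 or 6 | 69% |
| Blocks of 2, 4 or 6 | 70% (25.2 of 36) |

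The researcher makes every splint and so learns every assignment under any scheme. Small blocks would therefore raise predictability from history by about 9 to 11 percentage points over a single 18/18 list.

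**5. Number of envelopes**

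The synopsis gives 42 participants; sections 3.6 and 3.7 give 36. With 42, P(21/21) = 0.122 and the guess rate from one 21/21 list is 58.5%, so the conclusions do not change. The length of any list is nevertheless undefined until the two totals are reconciled.

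**The case against.** The protocol does provide safeguards. It specifies concealed allocation, someone other than the researcher selects the envelope, and the draw follows consent and an independent baseline assessment. If the selection is from a shuffled set, preparing it reveals its composition but not its order. Patients are diagnosed and referred by a surgeon, registered by counter staff, and judged against mostly factual criteria, which limits the room to act on a guess. The 18/18 appears only in the sample-size section and can be read as a planned 1:1 target, with simple used loosely for drawing lots.

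Most of this stands. The late draw by counter staff is a real safeguard, but a partial one: it does not remove what the recruiter may learn or influence by making the envelopes, and shuffling is nowhere stated. The reading of 18/18 as a target is fair, so the mismatch is a matter of wording to reconcile.

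A reader might infer something stronger: that the allocation must be either predictable to the recruiter or harmfully unbalanced. The documents do not support this. They do not say that the researcher fixes or knows an order, or that the pool is exactly 18 and 18. If it is, a perfect counter gains about 3 correct guesses in 36, with certainty for only about the last 2 patients. If allocation is truly simple, past assignments reveal nothing and the likely imbalance costs little.

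**Conclusion.** The point holds as a concealment weakness. One unblinded researcher screens, explains consent, prepares the envelopes and receives each assignment, and the protocol states none of the features that would make the envelopes proof against that person. This rests on the text alone and does not depend on any calculation. It does not allege that bias has occurred, and the size of any bias cannot be computed from the documents.

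The mismatch between simple randomisation and 18 per group is secondary. An exact 18/18 split has a 13% chance, but 14:22 keeps 95% efficiency. The guessing rates assume N = 36, a researcher who remembers every past assignment, and, for blocks, the assumed sizes above. The change should be made because it is cheap and must be in place at enrolment to be of use.

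**What to change.** **Concealment (section 3.8).** Replace the sentence on envelope preparation with text to this effect: a computer-generated sequence is produced, and placed in sequentially numbered, opaque, sealed envelopes, by an existing staff member with no screening, consent, treatment or assessment role; the counter staff hold the envelopes and open the next number only after consent and baseline assessment; the researcher is not told the sequence. The counter staff could also prepare them. The timing of the draw is already right and stays as it is.

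**Method (sections 3.6 and 3.8).** Choose one and word both sections to match:

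- keep simple randomisation and call 18/18 the expected split; or
- use one independently shuffled list of 18 A and 18 B, accepting that about 59% could be guessed from past assignments.

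If small permuted blocks are preferred, state their cost: about 68–70% guessable by a researcher who sees every assignment.

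**List length.** Reconcile 42 (synopsis) with 36 (sections 3.6 and 3.7) before the list is made.

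**Cost.** A protocol wording change and a one-off clerical task for existing staff, with no extra visits, patients or equipment. If enrolment has begun, apply it to all remaining participants.
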